#### Detection of Inflammatory Factors

Peripheral blood samples are collected to measure the levels of interleukin (IL)-1β, IL-6, tumor necrosis factor-α, IL-2, IL-4, IL-5, IL-8, IL-10, IL-12p70, IL-17A, interferon-γ, and interferon-α2. All sample processing and testing are conducted in strict accordance with the standardized operating procedures of the hospital’s clinical laboratory. Antibody chips are being employed to covalently bind highly specific inflammatory factor-capture antibodies onto chemically modified solid-phase chip substrates. Signal amplification is achieved through the use of high-affinity paired secondary antibodies, enabling the effective detection of trace cytokines. Furthermore, a standard curve is constructed using the detection signals of gradient dilutions of standards, allowing for accurate quantitative detection of inflammatory factors in human samples by standard curve fitting. All laboratory procedures are carried out by trained staff who are blinded to group assignments. Intra-assay and inter-assay coefficients of variation are consistently controlled below 10%, ensuring the reliability of the analytical results.

#### Assessment of Anal Function

The Wexner Anal Incontinence Score [21] is being used to assess the patient’s anal function before and 6 months after surgery. This score evaluates anal function and records incontinence in terms of dry stools, loose stools, gas, need for pads, and lifestyle changes (See Table S2 in Multimedia Appendix 1).

Assessments are conducted by trained research assistants who are blinded to group allocation and baseline scores. All assessors received standardized training prior to study initiation to ensure consistent administration and interpretation of the Wexner scoring system. At each assessment time point, the Wexner questionnaire is administered via a structured interview format. To further mitigate potential assessment bias, baseline scores are recorded prior to randomization and will be incorporated as covariates in the statistical models used to compare postoperative functional outcomes between the 2 groups.

### Follow-Up Plan

To ensure complete data collection, all participants will be contacted according to a standardized follow-up schedule. Automated text message reminders will be sent 2 days before each scheduled visit (postoperative days 3 and 7, and month 6), followed by a confirmatory telephone call 1 day prior. For the 6-month assessment, participants who are unable to attend an in-person will be offered a structured telephone interview to evaluate symptoms and functional status; if recurrence is suspected during the interview, an urgent in-person clinical evaluation, including DTI reassessment, will be arranged.

### Adverse Events Monitoring and Reporting

Adverse events (AEs) are defined as any unfavorable medical occurrence experienced by trial participants, irrespective of causal relationship to the study intervention. This includes newly emerging symptoms, clinically relevant abnormal laboratory findings, or exacerbations of preexisting medical conditions. A serious adverse event (SAE) is defined as any AE that fulfills at least one of the following criteria: results in death, is life-threatening, necessitates inpatient hospitalization or prolongation of existing hospitalization, results in persistent or significant disability/incapacity, or constitutes a congenital anomaly or birth defect.

All AEs will be graded according to the Common Terminology Criteria for Adverse Events, version 5.0, as follows: grade 1 (mild: asymptomatic or mild symptoms, no intervention indicated); grade 2 (moderate: minimal intervention indicated, interferes with activities of daily living); grade 3 (severe: medically significant but not immediately life-threatening, hospitalization indicated); grade 4 (life-threatening: urgent intervention required); and grade 5 (death). All AEs are systematically recorded at each study visit and during scheduled follow-up interactions. Nonserious AEs are documented in the case report forms and will be summarized in the final study report. SAEs must be reported to the principal investigator and the Institutional Ethics Committee within 24 hours of awareness, with a comprehensive written report submitted within 7 calendar days, followed by continuous documentation until event resolution or stabilization.

An independent Data and Safety Monitoring Board has been established to conduct periodic reviews of SAEs, interim safety data, and overall trial safety. The Ethics Committee maintains the authority to request supplementary information, recommend protocol modifications, or suspend the study based on safety evaluations. All investigators and study personnel have completed standardized training in AE/SAE identification, documentation, and reporting procedures prior to study initiation.

### Data Management and Quality Assurance

All study data will be managed through an electronic data capture system equipped with built-in logic checks and mandatory field validation to ensure data integrity, accuracy, and consistency. After entry, data will undergo dual independent verification, with systematic reviews conducted by data managers to identify outliers and address missing values. Data and Safety Monitoring Board will conduct periodic assessments of safety data, protocol compliance, and overall data quality. All study personnel have completed standardized training to maintain consistency and procedural rigor throughout data collection and evaluation processes.

### Statistical Plan

All analyses are prespecified. The primary analysis will follow the intention-to-treat principle. For the primary outcome, the 6-month recurrence rate will be analyzed using binary logistic regression, with results reported as an adjusted odds ratio and 95%
CI. Any clinically relevant baseline imbalances will be included as covariates, and missing recurrence data will be handled using multiple imputation. Secondary outcomes will be analyzed as follows: categorical items from the structured report will be compared using chi-square test or Fisher exact test; continuous structured report items will be compared using independent samples *t* tests or Mann-Whitney *U* tests, depending on normality; postoperative visual analog scale pain scores will be evaluated with a linear mixed model to assess group, time, and interaction effects, with results expressed as estimated marginal means and mean differences with 95%
CI; and inflammatory markers and Wexner incontinence scores will be compared at follow-up using *t* tests or Mann-Whitney *U* tests. To control for type I error across secondary outcomes, the false discovery rate procedure will be applied. Prespecified sensitivity analyses
using the per-protocol population and subgroup analyses
stratified by abscess complexity will also be performed. All statistical analyses
will be conducted using SPSS software (version 22.0), and statistical significance will be defined as a 2-sided *P* 
value <
.05
.

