**Methods:**

This study adopts a randomized, prospective, single-blind design. Ninety participants are being randomized into 2 groups: a DTI group and a conventional magnetic resonance imaging group. A structured report is being completed based on imaging of the perianal abscesses in terms of location, number, specific pus cavity alignment, thickness, and relationship to the surrounding muscles. In addition, the patient condition is being assessed, and corresponding surgical treatment is being performed. If the patient’s blood routine shows infection, cefuroxime sodium combined with metronidazole is being administered intravenously as an anti-infective therapy. Postoperatively, the primary variable is being assessed for recurrence rate at 6 months, and the secondary variables, including postoperative pain scores on days 3 and 7, peripheral blood inflammatory factors, and assessment of anal function, are being evaluated. Normally distributed continuous data will be presented as mean (SD) and analyzed using independent or paired *t* tests. Non-normally continuous data will be analyzed with rank-sum tests. Categorical data will be expressed as frequency (%) and compared using a chi-square test or appropriate nonparametric tests. Ordinal data will be analyzed using the Ridit test. A *P* value <.05 will be considered statistically significant.

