### Sample Size Calculation

The sample size was calculated based on data from a preliminary pilot study involving 20 patients with perianal abscesses (10 in each preliminary subgroup). Previous studies have reported an overall postoperative recurrence rate for perianal abscess of approximately 11.7% [17]. In the pilot study, the 6-month postoperative recurrence rate was 15% among patients who underwent conventional MRI–guided surgical treatment, while the recurrence rate was 5% in those who received preoperative DTI assessment combined with targeted surgical intervention. Using a 2-sided α level of .05 and a β level of .20, the sample size for the intervention (DTI group) and control (conventional MRI group) was estimated using Power Analysis and Sample Size software (version 11), resulting in N1=N2=41. Considering a 10% potential attrition rate during follow-up, the required sample size for each group was adjusted to 45 (41/0.9), leading to a total enrollment of 90 participants for the formal study.

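### The primary logistic model takes its covariates from observed imbalance and has no provision for about 9 expected events, so the covariate set is not prespecified and the odds ratio may not be estimable

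*Protocol article*

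**What the plan says.** The Statistical Plan section of the protocol article opens with the statement "All analyses are prespecified". For the primary outcome, "the 6-month recurrence rate will be analyzed using binary logistic regression, with results reported as an adjusted odds ratio" and a 95% CI. The covariate rule is "Any clinically relevant baseline imbalances will be included as covariates". Missing recurrence data are to be multiply imputed, under intention to treat, in SPSS 22.0.

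The section names no covariate, no criterion for imbalance and no limit on their number. It names no test for the treatment coefficient, and no penalised or exact method if an arm has no events. Fisher's exact test appears only for categorical structured-report items.

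The planning rates are in Sample Size Calculation: "the 6-month postoperative recurrence rate was 15% among patients" in the conventional MRI group, and "the recurrence rate was 5% in those who received preoperative DTI assessment". The calculation gives 41 per arm, raised to 45 for 10% attrition.

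**The concern.** There are two problems in the same sentences.

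- **The covariate set depends on the data.** A rule based on observed imbalance can be applied only after the baseline table has been seen, and clinical relevance is then a matter of judgement. Demographic and Baseline Data lists seven items (age, gender, race, height, weight, medical history, medication history), and other measures are also taken before surgery. Different defensible choices give different adjusted odds ratios and p-values for one primary endpoint.
- **The method suits the expected data badly.** Maximum-likelihood logistic regression is unreliable with very few events and has no finite treatment estimate when one arm has none. An empty DTI arm would be the most favourable result for the intervention, yet the promised odds ratio and interval could not then be reported as planned.

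**Working it through.** **Inputs.** Control rate 15%, DTI rate 5%, 41 evaluable and 45 randomised per arm, two-sided α .05 and β .20, all from Sample Size Calculation.

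**The plan's own figure.** The calculation is stated as "Using a 2-sided α level of .05 and a β level of .20", "resulting in N1=N2=41". With the pooled two-proportion formula,
n = [1.96·√(2·0.10·0.90) + 0.8416·√(0.15·0.85 + 0.05·0.95)]² / 0.10² = (0.8315 + 0.3521)² / 0.01 ≈ 140.1, that is 141 per arm. The stated 41 does not reproduce. That is a separate point; here it only explains why events are so few.

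**Expected events.**
- 45 per arm: 45 × 0.15 + 45 × 0.05 = 6.75 + 2.25 = 9.0 (5th to 95th percentile 5 to 14).
- 41 per arm: 6.15 + 2.05 = 8.2.
- Events per coefficient at 9 events: treatment plus one covariate, 9/2 = 4.5; treatment plus two, 9/3 = 3.

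**Chance of no DTI recurrence.** 0.95^45 = 9.9%; 0.95^41 = 12.2%. If the 41 observed DTI patients have no event, a logistic imputation model containing treatment meets the same empty cell.

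**A worked table, 0/45 vs 7/45, unadjusted.**
- Ordinary logistic fit: log odds ratio about −20 with a standard error in the thousands, Wald p = 0.996. The true estimate is minus infinity; the printed values depend only on where iteration stops.
- Fisher's exact test: p = 0.012.
- Likelihood-ratio test from the same model: G = 2{[7·ln(7/45) + 38·ln(38/45)] − [7·ln(7/90) + 83·ln(83/90)]} = 2(−19.45 + 24.60) ≈ 10.3, p = 0.0013.
- Firth-penalised: odds ratio (0.5 × 38.5)/(45.5 × 7.5) = 0.056, penalised likelihood-ratio p = 0.005.

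**Power at 45 per arm, control 15%, unadjusted.** This sums the binomial probabilities of all two-arm tables that reject at two-sided .05. Wald uses the log odds ratio divided by √(1/a + 1/b + 1/(n−a) + 1/(n−b)); an arm with no events counts as no rejection.

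| True DTI rate | Wald | Likelihood ratio | Score chi-square |
|---|---|---|---|
| 5% | 17.7% | 39.1% | 38.6% |
| 2% | 17.7% | 71.3% | 69.2% |
| 1% | 12.0% | 84.2% | 80.9% |

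Wald power does not rise as the true DTI rate drops from 5% to 2%, and it falls at 1%. The contrast is not at equal type I error: at 10% in both arms, chi-square rejects in 5.9% and Wald in 1.8%. Firth has 34.3% power at 15% vs 5%, with 4.6% rejection at 15% in both arms.

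**Other rates.** Primary Efficacy Outcome counts a newly developed fistula as recurrence, so the true rates may be higher. At an assumed 30% vs 10%, expected events are 45 × 0.40 = 18, the chance of an empty DTI arm is 0.90^45 = 0.9%, and Wald and chi-square power are 65% and 69%.

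**The case against.** The strongest reply is that the plan names no test. A reader might infer that a Wald test is planned, and so that the trial will be non-significant just when DTI works best. The documents do not support that: a likelihood-ratio test is an equally valid reading of logistic regression and keeps its power. What remains is that the odds ratio and interval fail in an empty arm whichever test is used. Wald is also the usual SPSS coefficient output and the usual basis for pooling over imputations.

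Second, the event count rests on planning rates that may be too low. The Introduction puts fistula after drainage at 30% to 50% within months to years. That figure does not carry over directly to radical resection at 6 months, but at higher rates the sparse-data problem largely goes away. This objection stands as a limit on size. It does not touch the covariate rule.

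Third, a statistical analysis plan may exist. It could list covariates, but only by replacing the rule that the protocol states.

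Two further inferences go too far. One is that the whole primary analysis is unspecified: the model family is fixed and only the covariate set is open. The other is that the abstract contradicts the Statistical Plan. Its line, "Categorical data will be expressed as frequency (%) and compared using a chi-square test", is generic by type of variable and does not name the primary outcome. Nor do the documents give a basis for saying how much covariates would raise the chance of a non-estimable model, since no candidates or threshold are listed.

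**Conclusion.** The point holds in two parts. The covariate rule conflicts with the claim of prespecification, for the covariate set, and leaves several possible primary results; this does not depend on any assumed rate. Ordinary logistic regression is also a poor fixed choice for about 9 events. At the plan's own rates there is roughly a 10% to 12% chance that the treatment odds ratio has no finite estimate and, if Wald inference is used, unadjusted power is less than half that of the score or likelihood-ratio test. The second part rests on 15% vs 5% and shrinks to a minor matter at 30% vs 10%. Most of the low power comes from the sample size, and a change of method does not cure that. The plan should be changed; the change is to the text of the analysis only.

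**What to change.** 1. Delete the imbalance rule. Name now either no covariate or at most one, measured before randomisation.
2. Make the primary analysis Firth-penalised logistic regression, or a score-based risk difference. In either case report a risk difference with its 95% CI.
3. State the test and interval, an imputation method that tolerates sparse or zero events, and a pooling method that suits the interval. Plain Rubin's rules combine estimates and standard errors; they do not pool profile-likelihood intervals.
4. As secondary wording, make the abstract's sentence on categorical data match the Statistical Plan.

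Cost: Firth regression may need R or an SPSS extension, and ad hoc adjustment for chance imbalance is given up. No design or data collection changes. Six-month follow-up is projected to end in April 2027, so the amendment can still be made before the outcome data are complete.

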### Management of Protocol Amendments

Any proposed amendment to the study protocol must be submitted for review and approval by the Ethics Committee prior to implementation. Approved amendments will be promptly reflected in the public clinical trial registry, and all investigators and relevant stakeholders will be formally informed. No protocol amendment shall adversely affect the rights, safety, or well-being of already enrolled participants. Any modification deemed to be of potential benefit to participants may only be implemented with Ethics Committee approval and, where applicable, following informed consent from the affected participants.

### Management of Participant Withdrawal

Participants retain the right to withdraw from the study at any stage without condition, and such withdrawal will not affect their future medical care. If a participant withdraws, data collected prior to withdrawal may be retained for use in the intention-to-treat analysis, provided that the participant has given consent for such use. If consent is not provided, the participant’s data will be deleted and excluded from the final analysis. The reason for withdrawal will be documented and reported. In cases where withdrawal is due to an AE, appropriate follow-up will be conducted until the event is resolved or stabilized.

## Results

The trial was registered on January 10, 2025, with the International Traditional Medicine Clinical Trial Registry (ITMCTR2025000068). The study obtained ethical approval in 2023. Participant recruitment began in April 2025 and is expected to continue until October 2026. Completion of the 6-month postoperative end point follow-up is projected by April 2027. Preliminary data analysis is planned for the second quarter of 2027, and the full study report anticipated to be submitted and published before the end of 2027. As of January 2026, a total of 37 participants had been enrolled. Results will be submitted for publication in a peer reviewed international journal. Findings will also be presented at relevant national and international conferences.

## Discussion

This study is designed to test the hypothesis that preoperative DTI, compared with conventional MRI, can provide superior visualization of perianal abscess extent and muscular involvement, thereby guiding more precise surgical excision and leading to a lower 6-month recurrence rate.

Currently, there is only 1 comparative study between DTI and MRI for perianal fistula [16], and no specific studies have been reported on the location depth, size, thickness of anal canal and rectum, and thickness of the levator ani muscle and internal and external sphincter of perianal abscesses. This protocol builds upon the feasibility shown in fistula imaging but shifts the focus to preoperative mapping of abscess morphology and infiltration—a critical gap in current clinical practice.

Perianal abscess is a common disease in the anorectal department, and surgery remains the most effective and complete cure treatment [22]. However, the relationship between the extent of abscess involvement and surrounding inflammatory infiltration is not determined before the operation, which can increase the risk of postoperative recurrence [23]. Although conventional MRI sequences have some diagnostic value in determining the extent of disease, they have limitations in distinguishing abscesses from inflammatory masses [24,25]. Therefore, a contrast agent that shows the characteristic edge enhancement of an abscess is often used in combination. However, there are increasing concerns regarding contrast injection, especially in patients with renal insufficiency, and the association between contrast exposure and nephrogenic systemic fibrosis has been emphasized [26]. Therefore, the search for alternative imaging techniques that do not use contrast agents has been an important topic, especially for high-risk patients, while ensuring that diagnostic value is maintained. DTI can clearly show the degree of infection infiltration, the extent of the abscess, and the relationship between the erosion of tissue and muscle around the pelvic floor [27,28]. This makes DTI essential for reducing the chance of recurrence. In addition, the fractional anisotropy and apparent diffusion coefficient values of the DTI parameters may play a role in assessing the extent and activity of the perianal abscess.

In this trial, 90 participants are being enrolled and divided into 2 groups, a DTI group and a conventional MR group, based on randomization performed before enrollment. “The primary variable, recurrence rate, and secondary variables, including structured reports, pain scores on postoperative days 3 and 7, peripheral inflammatory factors, and assessment of anal function, are being assessed at 6 months after surgery.” To ensure accurate and specific information, a structured report on the extent of perianal abscess infection based on DTI images is being prepared by both anorectal physicians and radiologists. Surgeons experienced in examining and operating on the lesions can provide valuable insights into the actual situation of the patient during surgery. By using a structured report, we aim to determine whether the test under consideration is effective and which of the 2 tests is more effective.

Although the recurrence rate of perianal abscesses after surgery is influenced by numerous factors, there is no doubt that the accuracy of the examination can greatly improve the success rate of surgery [29]. Currently, surgical treatment is the main method for perianorectal abscesses in clinical medicine. However, the location, number, specific shape of the abscess cavity, and its relationship with surrounding muscles of perianorectal abscess have a direct impact on the choice of surgical methods, which in turn will influence its prognosis [30]. Therefore, it is very important to pay attention to the preoperative diagnosis of such patients for the implementation of targeted and effective surgical treatment. Therefore, by using DTI MRI imaging sequences, we can scan the internal opening, the degree of infection and infiltration, the extent of abscess, and the relationship between the erosion of perianal tissues and muscles, to explore a new imaging method for the evaluation and diagnosis of perianal abscess. This approach can explore the application value of DTI in the diagnosis of perianal abscess. It can improve the accuracy of preoperative evaluation, reduce damage to the anal sphincter, reduce the recurrence rate, and improve the quality of life of patients.

DTI brings additional challenges to the diagnosis of perianal abscess. First, there is no uniform standard for measuring the thickness and ratio of the relevant muscles before surgery for perianal abscess, as well as the location, depth, and size of the abscess. To address this issue, relevant researchers will be trained by the director of radiology, relevant literature will also be reviewed to formulate unified standards. Second, monitoring MRI and operating room schedules is needed to identify potential study patients and appoint someone to manage the imaging data. Despite the challenges of such data collection efforts, many of the challenges of integrating research into clinical workflows can be overcome. DTI is a useful clinical tool for surgical planning and intraoperative guidance. By using DTI technology, we can gain a deeper understanding of the relationship between the internal orifice, the degree of infection infiltration, the extent of abscess, and the erosion of perianal tissues and muscles. These data may provide a basis for surgical treatment, and we hope that it will form a new technical standard for the diagnosis of perianal abscesses in the future.

It is hoped that the dataset being collected in this study will represent the objective parameters of the perianal muscular tissues and also effectively respond to the patient population we are eventually serve. As expected, due to regional ethnic differences, more data will need to be collected in the future, but it is expected that based on this study, the draft technical standards of DTI for perianal abscess diseases will be established, and new techniques for diagnosis and evaluation of perianal abscess will be developed and formed. This will serve the surrounding hospitals and reduce the postoperative recurrence rate and reoperation rate of perianal abscess patients.
